### Outcome measures, types of data and measurement techniques

We discriminate primary measures, which are essential to judge on the cancellation or conduction of the planned RCT, from secondary measures, which are all other data to be obtained.

#### Primary outcome measures

##### Appraisal by participating general practitioners

A structured interview will be held with partaking GPs. The main questions are: Would you once again participate in the trial? Why/why not? Do you have any ideas or proposals for programme improvements? In addition, age and sex of the physician and profile data of his or her practice are documented (urban or rural area, medical field, single handed practitioner or group practice, quarterly number of patients seen below 900, between 900 and 1500, above 1500).

##### Documentation of any undesirable event during the intervention

Any symptom or disease of any participant, which occurs during the intervention, is called an undesirable event. This definition is valid without reference to the fact, whether the intervention might be a cause or not. In case of an undesirable event, the participant promptly has to suspend exercise and to visit the surgery. The event has to be documented by a standardised report protocol, including the following judgements by the physician: medical/non-medical; caused/not caused by exercise; subject may/may not continue exercises.

##### Measures of drop-out

For each case of discontinued participation, the following reasons will be discriminated: medical reason (*r*_1_), change or misjudgement of inclusion or exclusion criteria (*r*_2_), subject's own decision (*r*_3_). After that, certain sets (groups) will be aggregated:

*A *– all participants who passed the baseline assessment

*DO*_*i *_– participants who drop out by reason *r*_*i*_

*DO *= *DO*_1 _∪ *DO*_2 _∪ *DO*_3 _– all participants who drop out

*A** = *A*\(*DO*_1 _∪ *DO*_2_) – adjusted set of participants (all participants not constrained to abort exercise by medical or trial criteria reasons)

*DO** = *A** ∩ *DO*_3 _– adjusted drop out group (participants who discontinue on their own decision). Members of this group will be asked for a personal reason (voluntary and open question), and also be asked to participate in the final assessment.

The following parameters are of special interest:

|*DO*| – total number of participants who drop out after the initial assessment

|*DO*_*i*_| – number of participants who discontinue for reason *R*_*i *_

|*DO**|/|*A**| – adjusted drop out rate

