#### Inclusion criteria

To be eligible for this study, patients have to be aged greater than or equal to 70 years. All participants need medical clearance from their GP to participate in the study. They have to be able to walk (with or without a walking aid) and to visit the practice of the GP for repeated consultations. Furthermore, participants have to be able to cooperate appropriately and to follow the instructions of the home-based exercise programme (according to their GP's judgement). Finally, all participants have to provide written informed consent.

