#### Exclusion criteria

Patients are excluded if the intervention doesn't fit into their schedule (e.g. because of a planned vacation). Patients are excluded for medical reasons if they suffer from untreated arterial hypertension or arterial hypertension despite antihypertensive medication (GP's judgement), from chronic heart failure (New York Heart Association (NYHA) grade III–IV), from an acute psychiatric disorder (e.g. depression), or from a severe consuming illness. Furthermore, patients are excluded, if they suffered a clinically relevant cardiovascular event (e.g. unstable angina pectoris, myocardial infarction, coronary angiography and/or angioplasty, cardiac surgery), a clinically relevant cerebrovascular event (e.g. stroke, recurrent TIA), any inpatient surgical procedure, or a deterioration of an insufficiently controlled diabetes mellitus (according to their GP's judgement) within the past 3 months, or if their HbA1c exceeds 10% (if available). Concurrent participation in another clinical trial is also an exclusion criterion.

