#### Criteria to decide on preparation of an RCT

In order to decide for or against the conduction of a randomised controlled trial on the new programme, three criteria based on primary outcome measures (see previous subsection) were set up. If one of them is met, the plans for an RCT will be cancelled:

**Criterion 1**. In the subsequent appraisal interview, more than 50% of participating GPs answer "no", when asked if they once again would participate in the trial, and the reasons for this answer seem unchangeable.

**Criterion 2**. More than 30% of the participants have to stop exercises for medical reasons, which the physician judges to be probably caused by the intervention.

**Criterion 3**. The adjusted drop out rate (see section "primary outcome measures – measures of drop-out") is above 60%, and no simple change of the criteria would clearly level down the adjusted drop out rate.

These three requirements will be analysed using binomial tests.

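### Criterion 3 drops all medical and eligibility-related stops, no criterion limits total drop-out, and the undefined border between reasons r2 and r3 can reverse the RCT decision

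*Protocol article*

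**What the plan says.** The section on measures of drop-out gives three reasons for stopping: medical (r1), "change or misjudgement of inclusion or exclusion criteria" (r2), and the subject's own decision (r3). The adjusted set `A*` is everyone assessed at baseline minus the r1 and r2 cases, described as "all participants not constrained to abort exercise by medical or trial criteria reasons". The adjusted drop-out group `DO*` holds "participants who discontinue on their own decision". The adjusted rate is |`DO*`|/|`A*`|. The same section lists |DO|, the "total number of participants who drop out after the initial assessment", as a parameter of special interest, with no threshold.

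Two eligibility criteria matter here. Under the exclusion criteria, "Patients are excluded if the intervention doesn't fit into their schedule (e.g. because of a planned vacation"). Under the inclusion criteria, "participants have to be able to cooperate appropriately and to follow the instructions of the home-based exercise programme", as judged by the GP.

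The section on criteria to decide on an RCT has three cancel rules. Criterion 1 concerns GPs' willingness to take part again. Criterion 2 applies if "More than 30% of the participants have to stop exercises for medical reasons, which the physician judges to be probably caused by the intervention". The last rule, criterion 3, applies if the adjusted drop-out rate is above 60% and no simple change of the criteria would clearly lower it. All three are to be analysed with binomial tests. The sample size of 90 is derived for criterion 3, with 45% assumed against 60%, power 80% and alpha 5%.

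**The concern.** The study exists to decide whether an RCT should follow, and criterion 3 is the rule for which it is powered. Two features weaken that rule.

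First, some stops count against no criterion: medical stops not attributed to the intervention, and all r2 stops. Whether patients of this age can complete the programme is part of feasibility, yet total non-completion is compared with nothing.

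Second, r2 covers a *change* in eligibility as well as a misjudgement. A participant whose schedule no longer accommodates the programme, or who proves unable to follow it, fits the wording of r2. The same person may also fit r3. Under r3 the stop raises the adjusted rate; under r2 the person disappears from it. Stops of this kind are what a feasibility study should detect, and a label assigned after the event would then influence the decision.

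**Working it through.** **Inputs from the protocol.** N = 90 assessed at baseline; threshold 60%; assumed rate 45%; power 80%; alpha 5%; binomial test. The article does not state sidedness or direction. It gives no expected share of r1 and r2 stops, so that share is an assumption, shown here at 20%, 30% and 40%.

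**Reproducing N = 90.** Exact binomial test of 60% against 45%, with 2.5% in the lower tail (two-sided 5%). At n = 90 the largest rejecting count is 44:

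- P(X ≤ 44 | 90, 0.60) = 0.0213
- P(X ≤ 44 | 90, 0.45) = 0.802

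No smaller n reaches 80% power, so the stated 90 is reproduced. Under this test, go means an adjusted rate significantly below 60%.

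**Effect of the label.** Take 50 of 90 participants stopping, with no r1 cases (illustrative).

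- All coded r3: 50/90 = 55.6%, P(X ≤ 50 | 90, 0.60) = 0.225. Not significantly below 60%.
- 13 of the 50 coded r2: `A*` = 90 − 13 = 77 and `DO*` = 50 − 13 = 37. 37/77 = 48.1%, P(X ≤ 37 | 77, 0.60) = 0.022. Significantly below 60%.

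With a one-sided 5% test, 10 recoded stops are enough: 40/80 = 50.0%, p = 0.0445. Behaviour is identical in each case; only the label differs.

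**Total non-completion compatible with go.** Let m be the number removed as r1 or r2, so that `A*` has n = 90 − m members. Let k be the largest number of r3 stops that still allows go. Total non-completion is (m + k)/90. On the observed-rate reading, k is 0.6n rounded down. On the test reading, k is the largest count with P(X ≤ k | n, 0.60) ≤ 0.025.

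| Removed (assumed) | n | k, observed rate ≤ 60% | Total | k, significantly below 60% | Total |
|---|---|---|---|---|---|
| 0 | 90 | 54 | 54/90 = 60.0% | 44 | 44/90 = 48.9% |
| 18 (20%) | 72 | 43 | 61/90 = 67.8% | 34 | 52/90 = 57.8% |
| 27 (30%) | 63 | 37 | 64/90 = 71.1% | 29 | 56/90 = 62.2% |
| 36 (40%) | 54 | 32 | 68/90 = 75.6% | 24 | 60/90 = 66.7% |

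**Side effect on power.** The 90 are counted at baseline, but the test runs on `A*`. At a true rate of 45%, the two-sided test has power 0.753 at n = 81, 0.691 at n = 72 and 0.616 at n = 63.

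**The case against.** The strongest reply is that the adjusted rate is explicit, prespecified and aimed at voluntary discontinuation, which suits the stated worry about the adherence of initially motivated participants. Someone who quits for lack of time has made a decision and is not constrained, so r3 is the natural code. The cooperation criterion concerns ability, not willingness, and the example given for schedule conflict is a planned vacation. |DO| and the count for each reason are already listed, so total drop-out can be calculated. Detailed coding rules may sit in the full protocol.

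Much of this stands. A reader might infer that scheduling and non-cooperation stops *are* r2 under the protocol. The text permits that coding but does not require it. A reader might also infer that medical stops are ignored altogether. They are not: criterion 2 catches those judged caused by the intervention once they exceed 30%.

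A third tempting reading is that relabelling always flips the decision. Take 58/90 = 64.4% falling to 43/75 = 57.3% after 15 stops are recoded r2. This crosses 60% only if the observed rate alone is compared with the threshold. Neither figure differs significantly from 60% in either direction (58/90: lower tail 0.83, upper tail 0.23; 43/75: 0.36 and 0.72), so with a binomial test that recoding changes nothing.

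What the reply does not remove is that the sets and the decision rule are fixed in this article, r2 explicitly includes a change of criteria, nothing shown separates it from r3, and listing |DO| attaches no consequence to it. The 50/90 example flips under the very test that yields N = 90.

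**Conclusion.** The point holds in a limited form. All r1 and r2 stops leave the criterion 3 rate, unrelated medical stops and all r2 stops enter no criterion, and the undefined border between r2 and r3 can reverse the powered decision.

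The size depends on two things the article does not give: the share removed as r1 or r2, and how the 60% rule and the binomial test combine. With an assumed 20–40% removed, go is compatible with total non-completion of up to about 68–76% on the observed-rate reading, or about 58–67% if the rate must be significantly below 60%. These are upper limits, not forecasts. A flat statement that the RCT can proceed with 65–75% non-completion would need its conditions: at least 13–35 of 90 removed (14–39%) on the observed-rate reading, or 33–52 of 90 (37–58%) under the two-sided test.

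Using an adjusted rate is legitimate. The weakness is that it is the only drop-out measure in the decision and one of its exclusions is open to interpretation.

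**What to change.** Before any drop-out is coded:

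1. Limit r2 to eligibility failures already present at baseline, and state that later schedule conflicts and non-cooperation are coded r3.
2. Report |DO|/|A| beside |`DO*`|/|`A*`|.
3. Repeat the criterion 3 test with all r2 stops counted as drop-outs, and state whether the go decision still holds.

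The cost is a change of wording on the drop-out form and one extra analysis. The reported rate may look slightly less favourable. The timing matters, because coding settled after the results are known cannot be shown to be neutral.

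Making 60% of |DO|/|A| a binding cancel rule would be a different criterion. That is a design choice for the investigators and is not needed to resolve this point.

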##### Measures of adherence

For the adjusted set of participants (*A**), measures of adherence are calculated:

• Number of consultation dates with the exercise therapist attended (personal and telephone exercise consultations)

• Number of activity units (walks, home exercises) documented in the activity log. Depending on the data available, corresponding numbers will also be calculated for *DO**.

#### Secondary outcome measures

##### Effect measures (week 0/1 and week 13)

To measure effects of the intervention on functional skills, every day physical activity, general health, frequency of falls and fear of falling, the following measures will be used:

a. Motor tests (in standardised order): timed up and go, chair rising, grip strength, tandem stand, tandem walk, sit-and-reach;

b. Telephone interview: PRISCUS-Physical Activity Questionnaire (PRISCUS-PAQ), Short Form 8 Health Survey (SF-8™ 4-week recall version), three month recall of frequency of falls, Falls Efficacy Scale – International Version (FES-I).

The "timed up and go" (TUG) test has been published in 1991 by Podsiadlo and Richardson [51] as a modified version of the "get up and go" test originally published by Mathias et al. [52]. The patient is timed while he rises from an arm chair, walks 3 meters, turns, walks back, and sits down again. The test is used to quantify mobility and coordination and has been demonstrated to be a sensitive and specific measure for identifying older adults who are prone to falls [53]. The "chair rising" test, a timed test of five repetitions of rising from a chair (arms folded across the chest) and sitting down, is used to measure lower body strength [54]. Grip strength of both hands is estimated using a vigorimeter [55]. The vigorimeter (Martin GmbH, Tuttlingen, Germany) is a pneumatic squeeze dynamometer that measures the pressure the hand is able to apply around a rubber ball (three attempts per hand). Adaptation to the individual hand anthropometry will be assured by using two different ball sizes. For test of standing balance, the subjects are asked to attempt to maintain their feet in the tandem position (heel of one foot directly in front of the other foot) for 10 seconds [56]. Three attempts are timed. For test of walking balance, the subjects are asked to attempt to walk heel of one foot directly in front of the other foot (tandem walk) for 8 steps. The number of performed steps is counted and documented (three attempts). A chair sit-and-reach test is used as a measure of hamstring flexibility [57]. The PRISCUS-PAQ has been developed to measure physical activity of the past 7 days in older adults (aged equal to or greater than 70 years) by telephone interview. General health will be assessed by the use of the Short Form 8 Health Survey (SF-8 4-week recall version). This instrument yields an 8-part profile of functional health and well-being. Two SF-8 composites can be calculated: the SF-8 physical component score (PCS) and the SF-8 mental component score (MCS). These scores are linear combinations of the eight items based on their respective importance for physical functioning and mental functioning. Higher scores represent better health status. The survey has demonstrated good reliability and validity [58]. Frequency of falls (three month recall) and fear of falling (Falls Efficacy Scale-International Version (FES-I) [59], will also be assessed by telephone interview.

##### Appraisal by participant (week 13)

Participants who completed the intervention will be asked to rate the utility of the following programme actions and devices (on a scale from 1 to 6 modified from [27]: introduction into the exercise programme, personal and telephone exercise consultations, pictorial guidebook, activity log, pedometer and elastic resistance bands. Participants will also be asked to rate the length of the programme, the frequency of phone and personal exercise consultations, and the recommendation for extent and intensity of exercise. Finally, an open question on concrete proposals for programme improvements will be asked.

##### Evaluation of exercise performance by the exercise therapist (week 13)

To identify exercises that are more and exercises that are less suitable for a home-based exercise programme, the performance of the patients will be assessed at the end of the programme in terms of whether they are doing their exercises correctly. All participants who completed the intervention will be rated by their exercise therapist for correctness of performance of all exercises that have been practised within the course of the programme. A three grade scale [60] is used: grade 1 indicates that the exercise is done so well that the goal of treatment is reached; grade 2 indicates that the exercise is not carried out correctly and the goal is not reached, but that no negative impact is to be expected; grade 3 indicates that the exercise is performed incorrectly and the goal is not reached and that there is reason to believe that the exercise might have harmful effects.

##### Focus group discussion with stakeholder representatives

As an additional qualitative measure, a focus group discussion with stakeholder representatives (investigators, exercise therapists, GPs, practice team, participants, drop outs) will take place at the end of the study.

### Statistical analysis and decision-making on RCT preparation

The main purposes for data analyses are the decision on a subsequent trial, the improvement of the programme and proper feedback to the participating individuals and physicians.

#### Criteria to decide on preparation of an RCT

In order to decide for or against the conduction of a randomised controlled trial on the new programme, three criteria based on primary outcome measures (see previous subsection) were set up. If one of them is met, the plans for an RCT will be cancelled:

**Criterion 1**. In the subsequent appraisal interview, more than 50% of participating GPs answer "no", when asked if they once again would participate in the trial, and the reasons for this answer seem unchangeable.

**Criterion 2**. More than 30% of the participants have to stop exercises for medical reasons, which the physician judges to be probably caused by the intervention.

**Criterion 3**. The adjusted drop out rate (see section "primary outcome measures – measures of drop-out") is above 60%, and no simple change of the criteria would clearly level down the adjusted drop out rate.

These three requirements will be analysed using binomial tests.

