#### Sample size

There are 3 criteria to decide if an RCT should be conducted. The power calculation is based on criterion 3, that means the adjusted drop out rate should be less than 60% to conduct an RCT. We expect more than half of the patients to actually complete the exercise programme and therefore assume a drop out rate of 45%. Given these assumptions a sample size simulation for a binomial test results in 90 patients (power = 80%, alpha = 5%).

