## Discussion

We conceptualised an activity programme for community-dwelling seniors, which

• on the individual level, contains multidimensional exercises according to accepted guidelines, and

• on the institutional level, establishes a cooperation between general practitioners and exercise therapists.

From the methodological point of view, clear criteria for the decision on the next step of development are given: A randomised controlled trial as phase III makes sense, if and only if phase II level of development was successful. Otherwise, the programme has to be changed fundamentally and phase II has to be passed through again. While the training effectiveness and patient eligibility are not expected to turn out as problems, another aspect may be crucial: The adherence of initially motivated participants. Both the design of the programme and the trial emphasise this aspect. The authors also were assured by a study of Armit and coworkers [61], which appeared after planning the trial: Inactive patients (50–70 years of age) from two GP practices were randomised into three groups, for behaviour change advice by the physician, or by the physician in collaboration with an exercise scientist. The third group received collaborative advice and a pedometer. Self-reported physical activity time increased for all groups, but the most intense intervention (collaborative advice and pedometer) yielded the highest probability for the patients to meet physical activity guidelines. In summary, a home-based exercise programme, approaching and supporting community-dwelling but mobility-restricted seniors via their GP ("surgery approach") and an exercise therapist, is object of research with regard to feasibility and acceptance. In case of success, a randomised controlled trial should examine the effects of the programme. After positive evaluation, a future implementation within primary medical care may take advantage from the flexibility and individuality of the programme.

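### Criterion 3 is worded as a condition for cancelling the RCT (drop-out above 60%), but the 80% power belongs to the opposite-tail test (drop-out below 60%), and the protocol does not say which one decides

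*Protocol article*

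**What the plan says.** Under Criteria to decide on preparation of an RCT, the protocol lists three conditions and states: "If one of them is met, the plans for an RCT will be cancelled". Criterion 3 is met when the adjusted drop-out rate "is above 60%, and no simple change of the criteria would clearly level down the adjusted drop out rate". The section closes with "These three requirements will be analysed using binomial tests". It gives no null hypothesis, direction, sidedness or decision count.

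The Sample size section bases the power on criterion 3 and restates it as a condition for going ahead: "the adjusted drop out rate should be less than 60% to conduct an RCT". It assumes a true rate of 45% and arrives at 90 patients for a binomial test with 80% power and 5% alpha. Sidedness is not given.

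Under Measures of drop-out, the denominator of the adjusted rate is |A*|: everyone who passed baseline, less those who stop for medical reasons or because of the trial criteria. The 90 counts participants at baseline, so |A*| equals 90 only if nobody stops for those reasons.

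On an unsuccessful phase II, the Discussion says: "Otherwise, the programme has to be changed fundamentally and phase II has to be passed through again".

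**The concern.** A condition for cancelling and a condition for proceeding, both set at 60%, are complementary only when the observed rate is compared with 60%. Once a significance test is attached, they separate. Testing whether drop-out is above 60% lets the RCT go ahead unless failure is shown. Testing whether it is below 60% lets the RCT go ahead only if success is shown. The first section uses the former wording and the second powers the latter.

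The decision on the RCT is the first stated purpose of the data analysis, and the primary outcomes are defined by their role in it. If the rule is settled only after the drop-out count is known, then over a wide range of counts the choice of reading settles the outcome.

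**Working it through.** **Inputs.** Null rate p0 = 0.60, assumed true rate p1 = 0.45, N = 90, power 80%, alpha 5% (Sample size); cancel if the rate is above 60% (criterion 3). X is the number of adjusted drop-outs. |A*| = 90 is assumed unless stated, and the waiver clause in criterion 3 is set aside.

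**1. Reproduce N = 90.** Take the largest c with P(X ≤ c | 90, 0.60) no greater than the allowed lower tail. Power is P(X ≤ c | 90, 0.45).
- Two-sided 5% (2.5% lower tail): c = 44, tail 0.0213 (45 gives 0.0347), power 80.2%. This matches the stated figure.
- One-sided 5%: c = 45, tail 0.0347 (46 gives 0.0543), power 85.5%. Here 80% power is first reached at N = 71 and holds from N = 75.

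So 90 patients at 80% power fits a lower-tail rejection of 60%, run as a two-sided 5% test.

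**2. Test the cancel condition as worded.** Take the smallest r with P(X ≥ r | 90, 0.60) no greater than the allowed upper tail.
- Two-sided 5%: r = 64, tail 0.0190 (63 gives 0.0321).
- One-sided 5%: r = 63, tail 0.0321 (62 gives 0.0517).

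**3. Use the observed rate.** 60% of 90 is 54, so above 60% means 55 or more.

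**4. Compare the rules.** Probability that the RCT goes ahead, by true drop-out rate:

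| Rule for criterion 3 | Ahead if X is | 45% | 60% | 65% |
|---|---|---|---|---|
| Show below 60%, two-sided 5% | ≤ 44 | 80.2% | 2.1% | 0.1% |
| Show below 60%, one-sided 5% | ≤ 45 | 85.5% | 3.5% | 0.2% |
| Observed rate not above 60% | ≤ 54 | 99.8% | 54.0% | 18.8% |
| Not shown above 60%, one-sided 5% | ≤ 62 | 100.0% | 96.8% | 81.1% |
| Not shown above 60%, two-sided 5% | ≤ 63 | 100.0% | 98.1% | 86.6% |

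**5. Counts in conflict with the powered test.**
- Cancel condition tested: 45 to 63 of 90 (50% to 70%) with two-sided tests, or 46 to 62 with one-sided tests. The chance of landing there is 19.8% (14.5%) at a true rate of 45%, 85.4% (79.9%) at 55% and 96.0% (93.3%) at 60%; one-sided figures in brackets.
- Observed rate used: 45 to 54, or 46 to 54 one-sided. At a true 60% the chance is 54.0% − 2.1% = 51.9%, or 54.0% − 3.5% = 50.5%.

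**6. Dependence on |A*|.** With a 2.5% lower tail, the critical count is 44 at |A*| = 90 (power 80.2%), 41 at 85 (76.1%) and 38 at 80 (71.4%).

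**The case against.** The criteria section never says that cancelling requires a significant result, so the upper-tail test is an inference from attaching a binomial test to the criterion as worded. A coherent reading is also available. The Sample size section glosses criterion 3 as a rate that must be below 60%, and the Discussion makes the RCT conditional on a successful phase II. Together these point to one lower-tail test. Sidedness and direction are also details that an article may leave to a fuller document, and this is a feasibility study with no treatment-effect claim.

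Most of this stands, and it limits the point. It does not remove it. On the coherent reading, 45 to 54 of 90 is still not above 60%, so the criterion does not cancel, yet it is not shown to be below 60%, so the powered test does not support going ahead. That is a mismatch between two things the article itself fixes, not an omitted detail.

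A reader might go further and infer that the rule as written usually lets a programme with 65% drop-out through. The documents do not support that. Taken literally, criterion 3 is met at 55 or more and cancels in 81% of trials at a true 65%, before the waiver clause. The 19% figure (100% − 81.1%) applies only if the cancel condition is what is tested, one-sided. Nor do the documents say how often the waiver clause would be used, so no figure can be put on it.

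**Conclusion.** The point holds in a limited form: the go/no-go rule stated for criterion 3 is not the rule that was powered, and nothing in the protocol says which decides. The size is a band of 45 to 63 drop-outs of 90 if the cancel condition is tested, or 45 to 54 if the observed rate is used. Both assume exact two-sided 5% tests and |A*| = 90; one-sided tests give 46 to 62 and 46 to 54. At the planning rate of 45%, the chance of landing in the wider band is 19.8% (14.5% one-sided), so the problem bites mainly if drop-out is worse than expected.

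Two further inferences should be resisted. The sample size is not wrong, since it reproduces. And the lower-tail rule should not be carried over to criterion 2: the power calculation covers criterion 3 only, so the documents support no new boundary there. What can be said of criterion 2 is that the test and its direction are equally unstated.

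A related inconsistency is that criterion 3 does not cancel unless "no simple change of the criteria would clearly level down the adjusted drop out rate", whereas the Discussion sends an unsuccessful phase II back through phase II. The two passages need reconciling.

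**What to change.** - **Criterion 3.** State one rule that matches the Sample size section: null hypothesis adjusted drop-out rate ≥ 60% against < 60%; exact binomial test at the level that gives N = 90 (two-sided 5%, that is, a 2.5% lower tail); RCT prepared only if the null is rejected. Tabulate the critical count by |A*| (44 if |A*| = 90).
- **Waiver clause.** Reconcile the provision for a simple change of criteria with the Discussion, so that it is clear what follows when the boundary is missed.
- **Criterion 2.** State only whether the 30% limit applies to the observed proportion or to a test, and in which direction. No new boundary is implied.

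This costs wording only and no extra patients, and should be settled before the drop-out data are seen. The price is a stricter decision than criterion 3 as now worded: at |A*| = 90, counts of 45 to 54 would no longer lead to an RCT. Power also falls below 80% if medical or criteria-related stops reduce |A*| (76.1% at 85, 71.4% at 80).
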